#### Long-term impact on parent's life

Mothers of two to five year old IVF twins experienced significantly higher levels of parenting stress and depression than mothers of IVF singletons and were less likely to obtain pleasure from their child and to be in paid employment [13,51].

#### Conclusion

Overall the current evidence confirms that post-neonatal costs are higher in IVF twins compared to IVF singletons. Reported results regarding health outcomes are inconclusive. Some studies were, however, not designed to detect significant differences between IVF twins and IVF singletons and probably lacked statistical power to detect differences. The available evidence is insufficient to estimate the long-term cost-effectiveness of SET strategies compared with DET strategies.

### Problem definition

In the Netherlands, long-term results from IVF children are currently lacking. It is timely to obtain an objective estimate of the long-term costs and health outcomes of twins and singletons born from IVF, to support the claim that twin pregnancies are a complication of IVF that should be prevented. Objective here means empirically based and taking account for sources of bias. To support the general believe that twin pregnancies are a complication of IVF and to make an evidence-based decision on the preferred embryo transfer strategy in IVF, both long-term costs and health outcomes of twins and singletons need to be estimated.

The TwinSing study is funded by the Netherlands Organisation for Health Research and Development (ZonMW), grant number 80-82310-98-09094. The study is approved by the Institutional Ethical Board of the Maastricht University Medical Centre (Ref no: 09-4-019) and the study is actively supported by the Dutch patient association Freya. The Ethical Board of the Maastricht University Medical Centre judged that the TwinSing study is not subject to the Medical Research Involving Human Subjects Act (WMO).

### Objective and research questions

The objective of the TwinSing study is to investigate the short (1-year) and long-term (5 and 18-year) costs, health outcomes and HRQoL of twins and singletons born from IVF. These results will be linked to a Markov model in which seven embryo transfer strategies are compared [32], to enable estimation of the long-term cost-effectiveness of SET strategies versus DET strategies.

The research questions are:

1. What are the short (1-year) and long-term (5 and 18-year) health outcomes of IVF twins and singletons?

2. What are the short (1-year) and long-term (5 and 18-year) costs of IVF twins and singletons?

3. What is the short (1-year) and long-term (5 and 18-year) cost-effectiveness of SET strategies versus DET strategies from a societal and healthcare perspective?

4. What is the value of additional information through research to reduce decision uncertainty?

## Methods/Design

### Design

A retrospective multi-centre (n = 5) cohort study will be performed, in which a representative sample of IVF twin children will be compared with a representative sample of IVF singletons with respect to mortality, health outcomes, HRQoL and costs from birth up to five years of life. Subsequently, future costs and health outcomes up to 18 years of life will be modelled. Input for the model will be based on the empirically collected data up to five years of life, existing databases, literature and expert opinion.

### Participants

The study population consists of twins and singletons born from IVF between 2003 and 2005, of whom parents have received IVF treatment in one of the five participating IVF centres in the Netherlands (Academic Medical Centre, Maastricht University Medical Centre, Radboud University Nijmegen Medical Centre, Erasmus Medical Centre and University Medical Center Utrecht). In the Netherlands, subfertility care is well-organized and centred in thirteen licensed clinics [52]. Hospitals without a licence can initiate and monitor the stimulation phase and refer to a licensed hospital for both oocyte retrieval and embryo transfer (satellite clinics) or for embryo transfer alone (transport clinics). Five of the 13 licensed centres and their collaborating transport- and satellite clinics, participate in the TwinSing study.

The *full sample *consists of all IVF twins and IVF singletons born between 2003 and 2005 of whom parents have received treatment in one of the participating centres. A total of 4,809 ongoing pregnancies were reported by these IVF centres between 2003 and 2005, of which - 3,789 singleton and 1,020 twin pregnancies. The actual size of the full sample will be somewhat lower since the reported figures are indicative; they are based on ongoing pregnancies not live births. Inclusion of an older cohort of IVF children is not considered to be valid, since the quality and results of IVF, neonatal and paediatric care have improved considerably during the last decade and since this study relies heavily on retrospective data collection, both from existing registries as well as from parents.

Data collection will primarily focus on the subgroup of children 'at risk' for health problems and on those children in which health problems have actually occurred. Therefore, for all children included in the full sample, information from the Perinatal Registry Netherlands (PRN) will be studied. Based on information from the PRN and the establishment of a clear set of criteria, all children at 'high risk' and a random sample of children at 'low risk' will be selected. All singleton children at 'moderate risk' and a random sample of twin children at 'moderate risk' will also be selected (see figure 1). Together, these children will form the basis for empirical data collection with respect to the first year of life, and will further be referred to as the *base sample*. Based on results up to the first year of life, the base sample of children will further be reduced for detailed data collection regarding the costs and health outcomes of the children up to five years of life and data estimation up to 18 years of life (further referred to as the *reduced sample*). Infant will be the unit of analysis. The selection of IVF twin children of a pair for inclusion in the base sample and reduced sample will occur independently.

**Figure 1 F1:**
[figure not shown]
**Risk stratification and sample size (figures are indicative)**.

In order to sufficiently take account of heterogeneity within the children who experienced health problems, it is expected that costs and outcome data of at least 100 singletons and 100 twin children with health problems are required in the reduced sample. Regarding children without health problems, data of 50 singletons and 50 twin children is expected to be sufficient, as variance will be considerably lower. Taking sufficiently account of missing data in all phases of data collection (5% for risk stratification, 10% for data collection up to one year of life and 20% for data collection up to five years of life), a sample size of 175 twin children with health problems, 56 twin children without health problems, 104 singletons with health problems, and 56 singletons without health problems, is required for the reduced sample.

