**Methods/Design:**

A multi-centre cohort study will be performed, in which IVF singletons and IVF twin children born between 2003 and 2005 of whom parents received IVF treatment in one of the five participating Dutch IVF centres, will be compared. Data collection will focus on children at risk of health problems and children in whom health problems actually occurred. First year of life data will be collected in approximately 1,278 children (619 singletons and 659 twin children). Data up to the fifth year of life will be collected in approximately 488 children (200 singletons and 288 twin children). Outcome measures are health status, health-related quality of life and costs. Data will be obtained from hospital information systems, a parent questionnaire and existing registries. Furthermore, a prognostic model will be developed that reflects the short and long-term costs and health outcomes of IVF singleton and twin children. This model will be linked to a Markov model of the short-term cost-effectiveness of single embryo transfer strategies versus double embryo transfer strategies to enable the calculation of the long-term cost-effectiveness.

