#### Empirical data collection up to the first year of life

Data with respect to the first year of life will be collected in children of the base sample. Based on figures reported by the PRN over 2004 [12] and expert opinion it is expected that approximately 1,278 children will be included in the base sample. The estimated number of children in each risk category is shown in figure 1.

Cost and outcome data up to the first year of life will be obtained from the hospital information systems of the relevant hospitals, existing registries and, if necessary, patient charts will be reviewed to obtain relevant cost and outcome data. The following registries will be used: 1) the PRN, which encompasses information regarding mother, pregnancy and the newborn; 2) the National Medical Registration (LMR), which registers medical and administrative data of all patients who have been admitted or have received outpatient treatment in Dutch hospitals; and 3) the Netherlands Twin registry (NTR), which follows a cohort 72,000 twins regarding pre- and perinatal information, health status, growth and motor development and behaviour [53,54]. As we intend to collect follow up data directly from hospital records, the use of data from the LMR will be optional. It is expected that data collection up to the first year of life will succeed in 90% of these children.

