#### Empirical data collection from the first year of life up to the fifth year of life

Based on empirical collected costs and outcome data up to the first year of life, a subgroup of children will be selected for data collection up to the fifth year of life, referred to as the reduced sample. All children with resolved or persistent health problems, and a random sample of children without resolved or persistent health problems will be included in the reduced sample. Assuming that missing data are completely at random, resolved and persistent health problems are expected in 4.0% of the singletons and in 12.5% of the twin children. Approximately 488 children will be included in the reduced sample (see figure 1). Besides the data sources mentioned above, cost and outcome data up to the fifth year of life will also be gathered by means of a parent questionnaire. The questionnaire will consist of three parts, the first part referring to the past, the second part referring to the present and the third part referring to expectations regarding the future. The parent questionnaire will focus on health outcomes, HRQoL and costs.

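### The 391 children given as the required reduced sample are the number expected to have five-year data after the 20% loss; the number to select is the 488 stated elsewhere

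*Protocol article*

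**What the plan says.** The sample-size paragraph of the Participants section (below Figure 1) first sets minima. For children with health problems, "at least 100 singletons and 100 twin children with health problems are required in the reduced sample". For children without them, "data of 50 singletons and 50 twin children is expected to be sufficient". It then lists the losses expected in each phase: "5% for risk stratification, 10% for data collection up to one year of life and 20% for data collection up to five years of life". Having allowed for these, it gives as the size required for the reduced sample "a sample size of 175 twin children with health problems, 56 twin children without health problems, 104 singletons with health problems". The fourth group, singletons free of such problems, is put at 56.

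The section on data collection from the first to the fifth year of life says: "Approximately 488 children will be included in the reduced sample (see figure 1"). It describes the reduced sample as the children chosen for follow-up to year five: all children with resolved or persistent health problems, plus a random sample of the others. The abstract says: "Data up to the fifth year of life will be collected in approximately 488 children (200 singletons and 288 twin children").

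**The concern.** The four required numbers sum to 391, and the other two places give 488 for the sample of the same name. The gap is 97 children, too large for rounding or for the word approximately.

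The direction of the gap matters. A size described as allowing for missing data should be the larger number, the one to start from. Here it is the smaller one. If 391 is already net of the five-year loss, a team that draws its random sample to these figures loses another 20% from a number with no room for it. The group sizes for children without problems are a choice the team must make, and 56 is the only figure for them in the visible text.

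**Working it through.** **Inputs.** Participants section: "3,789 singleton and 1,020 twin pregnancies", hence 1,020 x 2 = 2,040 twin children; losses of 5%, 10% and 20%; minima of 100 and 50. Risk stratification section: 8% of singletons at moderate or high risk, all taken, plus 10% of the rest; twins 20% high risk (all taken), 30% moderate (30% taken), 50% low (10% taken). Section on years one to five: health problems in 4.0% of singletons and 12.5% of twin children.

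**Step 1, reproduce the base sample, to test the chain.**
- Singletons: 3,789 x 0.95 = 3,599.6; x (0.08 + 0.92 x 0.10) = x 0.172 = 619.1 (stated 619).
- Twins: 2,040 x 0.95 = 1,938; x (0.20 + 0.30 x 0.30 + 0.50 x 0.10) = x 0.34 = 658.9 (stated 659).

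**Step 2, compare the totals.** 175 + 56 + 104 + 56 = 391, and 488 x 0.80 = 390.4. By group, (104 + 56)/0.80 = 200 singletons and (175 + 56)/0.80 = 288.75 twins (stated 200 and 288).

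**Step 3, follow each cell through the losses.**

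| Cell | Before the 20% loss | After it | Stated |
|---|---|---|---|
| Singletons with problems | 3,789 x 0.95 x 0.04 x 0.90 = 129.6 | 103.7 | 104 |
| Twins with problems | 2,040 x 0.95 x 0.125 x 0.90 = 218.0 | 174.4 | 175 |
| Singletons without | 200 - 130 = 70 | 56 | 56 |
| Twins without | 288 - 218 = 70 | 56 | 56 |

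The stated cells match the column after the loss, within rounding. The column before it sums to 130 + 218 + 70 + 70 = 488.

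**Step 4, try the other direction.** If the stated numbers were the minima inflated for loss, 100 would become 100/0.80 = 125, or 100/(0.95 x 0.90 x 0.80) = 147 rounded up. Neither 104 nor 175 arises this way. The 56 can be read as 50/0.90 = 55.6, rounded up, but that covers only the 10% first-year loss. Covering both later losses gives 50/(0.90 x 0.80) = 69.4, that is 70, which agrees with Step 3.

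**Step 5, the consequence for the randomly drawn groups.** Selecting 56 leaves 56 x 0.80 = 44.8 with data, against 50. To expect 50, the team must select 50/0.80 = 62.5, so 63. Selecting 70 leaves 56.

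**The case against.** Three points on the other side have force.

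First, the selection rule protects the children with problems. A reader might multiply 104 by 0.80, get 83 singletons with problems and conclude that the study will miss its minimum of 100. The documents do not support this. All children with health problems enter the reduced sample, so 104 and 175 cannot act as quotas. Following the rule, about 130 and 218 are approached and about 104 and 174 yield data. Twins with problems would stay above 100 even if 175 were a quota (175 x 0.80 = 140).

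Second, a reader might charge the abstract with overstating the first-year sample too, since 1,278 x 0.90 is about 1,150. That does not stand as an error. The section on the first year calls 1,278 the number included and adds in the same place: "It is expected that data collection up to the first year of life will succeed in 90% of these children". Nothing contradicts it, and the abstract does not call either number the analysed one.

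Third, the split 130/70/218/70 is not printed in the visible text. The two 70s come from subtraction. The 130 and 218 treat 4.0% and 12.5% as shares of the whole full sample and assume that every such child reaches the base sample, although only fractions of the moderate-risk twins and low-risk children are drawn. Figure 1 is not shown, is captioned as indicative and may already give the split. This limits how firmly the cell numbers can be written in. It leaves untouched the contradiction between 391 and 488, which needs none of these assumptions.

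**Conclusion.** The sample-size paragraph is wrong as worded. It presents the expected yield after the five-year loss as the loss-adjusted size of the reduced sample, while two other places give about 488 for that sample. The contradiction and the 0.80 ratio follow directly from the stated figures. The cell-by-cell account also rests on reading the health-problem rates as shares of all children, which the match to 104 and 175 supports but does not prove. The starting counts are themselves indicative, because they are ongoing pregnancies rather than live births.

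The exposure is limited to the two groups without problems: about 45 with data per group instead of at least 50, if 56 are drawn. For a mean in such a group the standard error would be sqrt(50/44.8) = 1.06 times that at 50, with the same spread. The 488 design is sound and is expected to meet all four minima (about 104, 174, 56 and 56). The point is of moderate importance: a stated sample size needs correcting, but the design does not.

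**What to change.** In the sample-size paragraph, describe 175/56/104/56 (391) as the numbers expected to have five-year data. Add that about 488 children are to be selected to reach them: by the plan's own rates about 218 + 70 twin children and 130 + 70 singletons, to be checked against Figure 1 before they are printed. State the random draw of children without problems explicitly as a number to select, about 70 per group and not fewer than 63. In the abstract, say that about 488 are selected for follow-up to year five and about 391 are expected to have data.

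This changes text only. The selection rules and analyses stay as they are. The one cost is that the abstract then shows the smaller number expected to have five-year data.

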### Data collection

#### Data collection full sample

The five participating IVF centres will each provide a dataset consisting of mothers who have had an effective IVF treatment and gave birth to a singleton or twin between 2003 and 2005. The data received from the IVF centres will be linked to the PRN database, which encompasses information regarding mother, pregnancy and newborn. The data will be matched to the PRN database based on the birth date of the mother, parity of the mother, (an estimation of) the birth date of the child(ren), and whether it was a singleton or twin birth.

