#### Risk stratification

Risk stratification will be applied to all children in the full sample. Based on information from the PRN regarding the pregnancy (weeks gestation) and the newborn (birth weight, Apgar score and congenital malformations), the children of the full sample will be assigned to a risk profile (i.e. 'low risk', 'moderate risk' or 'high risk'). The risk stratification criteria are: 1) prematurity (< 37 weeks gestation); 2) 5-minute Apgar score (< 7); 3) congenital malformations; and 4) birth weight (< 2,000 gram) (see figure 1). The criteria are set such that the probability of a false negative, i.e. the chance that a child 'at risk' is assigned to the low risk category, is minimized. A child will be assigned to the 'moderate risk' category if the child is born before 37 weeks gestation, has a Apgar score below seven, or has a congenital malformation. If the child also has a birth weight below 2,000 gram, the child will be assigned to the 'high risk' category. The other children will be assigned to the 'low risk' category. Based on figures reported by the PRN [12] and expert opinion it is expected that approximately 8% of the singletons will be assigned to the 'moderate risk' or 'high risk' category. All 'moderate risk' and 'high risk' singletons and a random selection of 10% of the remaining ('low risk') singletons will be included in the base sample. Based on figures reported by the PRN [12] and expert opinion it is expected that half of the twin children is born before 37 weeks gestation, have a low APGAR score or a congenital malformation. Approximately 40% of these twin children will also have a low birth weight (20% of all twin children) and will be assigned to the 'high risk' category. The other 60% of these twin children will have a birth weight above 2000 gram (30% of all twin children) and will be assigned to the 'moderate risk' category [12]. All other children (50% of all twin children) will be assigned to the 'low risk' category. All twin children of the 'high risk' category, a random selection of 30% of the 'moderate risk' category and a random selection of 10% of the 'low risk' category will be included in the base sample.

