### Data analysis

#### Empirical data

Health outcomes of the singleton and twin children, including mortality, perinatal outcomes, morbidity and developmental and behavioural problems will be analysed. Subsequently, health outcomes will be expressed in QALYs. QALYs will be calculated based on mortality and HRQoL data retrieved from both the EQ-5D and the HUI. Costs will be calculated by multiplying volumes of resource use with the cost price. Cost prices will be obtained from the Dutch manual of costing studies [60] and financial departments of the participating centres. For cost prices that are not readily available, such as institutional care, special education and school absence, cost price calculations will be performed.

Descriptive statistics will be used to describe the main characteristics and outcomes of IVF singleton and twin children. The base sample and the reduced sample are not representative of the Dutch IVF population as a consequence of the risk stratification and the random selection of subsamples of healthy children. Therefore, before analysing the data, the proportions of high, moderate and low risk singletons and twin children will be adjusted, to properly reflect the ratios in the original population.

Results will be presented with and without stratification for maternal age and parity. The issue of selection (information) bias will be investigated explicitly by comparing PRN data of children with (completely) missing data with PRN data of children included in the analysis.

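### Cohort entry needs a registry match that may rest on an estimated birth date; if preterm births link less often, the planned selection-bias check cannot show it

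*Protocol article*

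**What the plan says.** - **Linkage (Data collection full sample).** Each centre supplies a dataset of mothers. These records are matched to the PRN on four keys: the mother's birth date, and "parity of the mother, (an estimation of) the birth date of the child(ren), and whether it was a singleton or twin birth".
- **Stratification (Risk stratification).** Children receive a risk category "Based on information from the PRN regarding the pregnancy (weeks gestation) and the newborn" (birth weight, Apgar score, malformations). Prematurity is the first criterion. The article expects "approximately 8% of the singletons will be assigned to the 'moderate risk' or 'high risk' category". For twin children it expects half to be at risk: 20% high and 30% moderate.
- **Allowance for loss (Participants, text below Figure 1).** The planned losses are "5% for risk stratification, 10% for data collection up to one year of life and 20% for data collection up to five years of life".
- **Bias check (Data analysis, Empirical data).** Selection bias is to be examined by "comparing PRN data of children with (completely) missing data with PRN data of children included in the analysis". The same section adjusts the risk proportions to those of the population from which the samples were drawn.

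**The concern.** The PRN match is the only route into the study. A child whose record does not link has no risk category and cannot be selected.

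One key may be an estimated birth date. If that estimate is a due date, its error for a given child is roughly the degree of prematurity: a child born at 30 weeks would be about ten weeks away from it. With a limited window, failure to link would then be related to the main risk criterion.

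Two features of the plan leave this open. The loss is budgeted as one flat percentage, and the stated bias check uses data that do not exist for unlinked children. At stake are the at-risk shares in each group, the absolute twin-singleton difference in health problems and costs that feeds the embryo-transfer model, and the number of singletons with health problems, where the plan has little slack.

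**Working it through.** **Inputs from the article.** Ongoing pregnancies: "3,789 singleton and 1,020 twin pregnancies", so 3,789 singletons and 2 × 1,020 = 2,040 twin children. At-risk share p: 0.08 and 0.50. Health-problem rate h: 4.0% and 12.5%. Sampling fractions: all at-risk singletons and 10% of low-risk singletons; for twin children 100% of high, 30% of moderate and 10% of low risk. Losses: 5%, 10%, 20%. Minimum with health problems in the reduced sample: 100 per group.

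**Step 1: reproduce the plan.**
- Singletons: 3,789 × 0.95 × (0.08 + 0.92 × 0.10) = 619.1 (stated 619).
- Twin children: 2,040 × 0.95 × (0.20 + 0.30 × 0.30 + 0.50 × 0.10) = 658.9 (stated 659).
- Total: 1,278.0 (stated 1,278).
- With health problems after all losses: 3,789 × 0.95 × 0.04 × 0.90 × 0.80 = 103.7 (stated 104), and 2,040 × 0.95 × 0.125 × 0.90 × 0.80 = 174.4 (stated 175).
- Reduced sample: adding 70 children without health problems per group (inferred from 70 × 0.80 = 56) gives 199.6 + 288.0 = 487.6 (stated 488).

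The figures reproduce with the same 5% loss applied to every stratum and to both groups.

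**Step 2: upper bound within the 5%.** If the whole 5% in twin children is linkage loss among at-risk children, 5 of 50 points go, which is 10% of that stratum. Their share becomes (50 − 5)/(100 − 5) = 47.4%. If loss is random, it stays at 50%.

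**Step 3: assumed scenarios.** The article gives no match rate by gestation, so the loss rates below are assumptions. Let a be the loss among at-risk children and l the loss among low-risk children, the same in both groups. All health problems are placed in the at-risk stratum.
- Linked fraction L = p(1 − a) + (1 − p)(1 − l)
- At-risk share = p(1 − a)/L
- Health-problem rate = h(1 − a)/L
- Expected number with health problems and five-year data = N × h × (1 − a) × 0.90 × 0.80

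| l / a | Overall loss, single / twin | At-risk share, single / twin | Health-problem rate, single / twin | Difference (points) | Ratio | Number with problems, single / twin |
|---|---|---|---|---|---|---|
| 5% / 5% (plan) | 5.0% / 5.0% | 8.0% / 50.0% | 4.00% / 12.50% | 8.50 | 3.12 | 103.7 / 174.4 |
| 0% / 10% | 0.8% / 5.0% | 7.3% / 47.4% | 3.63% / 11.84% | 8.21 | 3.26 | 98.2 / 165.2 |
| 5% / 10% | 5.4% / 7.5% | 7.6% / 48.6% | 3.81% / 12.16% | 8.35 | 3.19 | 98.2 / 165.2 |
| 5% / 20% | 6.2% / 12.5% | 6.8% / 45.7% | 3.41% / 11.43% | 8.02 | 3.35 | 87.3 / 146.9 |
| 5% / 30% | 7.0% / 17.5% | 6.0% / 42.4% | 3.01% / 10.61% | 7.60 | 3.52 | 76.4 / 128.5 |

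The absolute difference shrinks, while the ratio rises. The last three rows exceed the plan's 5% in both groups.

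**Step 4: slack.** Linkage loss among children with health problems takes the expected count below 100 once it exceeds 1 − 100/(3,789 × 0.04 × 0.72) = 8.4% in singletons, and 1 − 100/(2,040 × 0.125 × 0.72) = 45.5% in twin children.

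**Step 5: what the bias check can see.** It needs PRN data on the missing children. Children lost after linkage have them; children who never linked do not. This holds whatever the match window.

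**The case against.** The strongest reply is that the mechanism is not in the document. The wording of the key suggests that the actual date is used where known. Nothing says that the estimate is a due date, how many records depend on it, or what window applies. Such detail is commonly left to a full protocol, which is not shown, and the PRN's gestational age means that matching on conception could already be the method. Date is one of four keys; the mother's birth date, parity and plurality may carry a match with a wide window. Plurality discriminates more for twins, so a twin match may tolerate more date error. Some at-risk children qualify by Apgar score or malformation at term and have no date problem.

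All of this stands. A reader might infer that preterm children are the ones most likely to be lost; the article does not establish that. Nor does it support more loss among twins for a given preterm child: the contrast is one of group composition only (50% against 8%).

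Two further readings go too far. Placing the whole 5% on the high-risk twin stratum would cut its share from 20% to (20 − 5)/95 = 15.8%, but that stacks worst cases, and the 5% is not said to be all linkage failure; it could include linked records with missing items. Nor does the article say that the re-weighting target is the linked sample, so it cannot be taken as fact that the weights carry the loss forward. The statement "Assuming that missing data are completely at random" introduces expected rates for planning and is not an analysis assumption.

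Centre counts by plurality and the expected risk shares would give a rough benchmark against which a large shortfall might show. But those counts are of ongoing pregnancies, and the shares rest partly on expert opinion. The reply does not remove the limit of the bias check, which needs no assumption about the date.

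**Conclusion.** The point holds in conditional form. Established from the text: entry requires a PRN match, the child's birth date may be an estimate, one uniform loss is budgeted, and the only stated selection-bias check cannot describe unlinked children. Conditional on a due-date estimate and a limited window: preterm births link less often, and group-level loss is larger in twin children.

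The size of any bias is unknown. It is zero if loss is random. Within the planned 5%, the upper bound for the at-risk twin share is a fall from 50% to 47.4%. In the matching scenario, the health-problem difference goes from 8.50 to 8.21 points, assuming that all health problems arise in the at-risk stratum and that the results reflect the linked sample. It would be wrong to conclude that twin costs will be understated; that is only the likely direction on the absolute scale if the conditions hold, and the twin-to-singleton ratio moves the other way. The case for acting is that the safeguard is cheap and the present check has a gap, not that bias has been shown.

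**What to change.** 1. Where the actual birth date is not held, match the centre's treatment date (embryo transfer or oocyte retrieval; assumed to be held) to PRN birth date minus PRN weeks of gestation. Use a tolerance fixed in advance and a constant offset for how gestation is counted. Keep the mother's birth date, parity and plurality as keys. Provided gestation is recorded equally well at all gestations, prematurity then no longer affects the match.
2. Report linkage rates by centre and plurality.
3. Add to the selection-bias check a comparison of linked with unlinked mothers on IVF-centre data: maternal age, parity and plurality. The match already requires the mother's birth date, parity and plurality. This comparison cannot show gestation directly, but a lower linkage rate in twins would be a warning sign.

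The cost is a little more linkage programming and one further table. No new data collection is needed if the treatment dates are held.
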